Symptom Checklist-90-R		Xe		Xe	Xe
WHO Well-Being Index		Xe		Xe	Xe
Sheehan Disability Scale		Xe		Xe	Xe
Adverse events			Xp	Xp	
Behaviour log			Xe		

*Xe* electronic collection of data, *Xp* paper collection of data

*WHO* World Health Organisation

^a^Improving Access to Psychological Therapies

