### Support person and support manual

Each trial participant is contacted over the telephone by a support person once a week during the 9 weeks of intervention. Each telephone contact should take about 10 min and a maximum of 1.5 h for the whole intervention period. The purpose of the contact is to secure and assess compliance and also to assist the participant’s adherence to the programme. The support person follows a support manual for the amount, type, and content of the support given. The support person must not engage in a psychotherapeutic dialogue with the participants. The support person who performs all the initial interviews and baseline assessments will also support the 32 participants in the experimental group. The reason for this is to optimise the alliance between the participants and the support person.

The manual for the support person prepared by the company behind the Danish version of FearFighter™ was tested by us, the trial investigators, and found to be too unspecific and vague for having standardised support in our trial. Therefore, we prepared our own manual with specific instructions for the support at each session in FearFighter™. None of the instructions in our manual are in conflict with, or violate the general instructions in, the support manual by the Danish company. Both the original support manual and our manual are written in Danish and can be obtained upon request.

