## Outcomes

### Feasibility outcomes

The primary feasibility outcome is the proportion of randomised participants out of all eligible people. Eligible participants are those who fulfil our inclusion criteria. The secondary feasibility outcome is compliance, defined as the number of participants completing at least six of the nine planned FearFighter™ sessions in the experimental group. FearFighter™ will automatically register time for login and save the exercises that have been completed. The support person sees a tracking log on the administration webpage for FearFighter™ for each participant and the compliance will be assessed during the weekly telephone calls with the experimental participants and summed-up at the end of the trial interview.

Participants who complete six or more sessions in FearFighter™ but who fail to show up for post-treatment assessment are still regarded as completers in the feasibility outcome. If the participants complete less than six sessions they will be regarded as noncompleters (dropouts).

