Serious adverse events and other untoward events that require hospitalisation, are life-threatening, or result in death are collected following the SPIRIT recommendations [20]. All adverse and untoward events will be categorised and summated. Finally, the proportion in the groups of experimental and control participants who are compliant with the randomised intervention, defined as the lack of any psychological treatment during the 9-week intervention period, will be registered. At follow-up, it will be registered if participants have been engaged in psychological treatment since the end of the trial, although no restrictions will be imposed on the participants during the follow-up period.

All scores will be compared between the two groups at post-treatment (week 10) and at follow-up (week 37). Serious adverse events and other untoward events will be gathered during the intervention for the intervention group and at post-treatment for both the control and the intervention groups.

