Number of participants complying at least 6/9 FearFighter™ sessions/ randomised participants	Not relevant	Proportion	Test analogous to the above feasibility outcome with the difference that now we want to secure that the sample is not from a population being less than 60 % compliant
Exploratory outcome			
Number of participants who no longer fulfil the diagnostic criteria for an anxiety disorder	MINI	Proportion	Fisher’s exact test and logistic regression adjusted by the protocol-specified stratification variable (the result of the latter test is the primary of the 2 tests)
Severity of anxiety	BAI	Continuous	The general linear univariate model (GLM) taking stratification variables and baseline BAI into account
Psychological distress and psychopathology	SCL-90-R	Continuous	GLM taking stratification variables and baseline SCL-90-R into account
Positive well-being	WHO-5	Ordinal	The proportional odds model for ordinal response taking stratification variables and baseline WHO-5 into account (if conditions are not fulfilled, then nonparametric Mann-Whitney)
Functional impairment	SDS	Continuous	GLM taking stratification variables and baseline SDS into account.
Number of randomised receiving psychological treatment during the 9 weeks	Interview	Proportion	Fisher’s exact test and logistic regression adjusted by the protocol-specified stratification variable (the result of the latter test is the primary of the 2 tests).
Number of participants with one or more adverse event	Interview	Proportion	Fisher’s exact test and logistic regression adjusted by the protocol-specified stratification variable (the result of the latter test is the primary of the 2 tests)

*BAI* Beck Anxiety Inventory, *MINI* Mini International Neuropsychiatric Interview*, SCL-90-R* Symptom Checklist-90 revised, *SDS* Sheehan Disability Scale, *WHO* World Health Organisation

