We have added one additional exploratory outcome, namely the proportion of participants in the experimental and control groups who are compliant with the randomised intervention, defined as the absence of any psychological treatment during the 9-week intervention period. This outcome, as well as the proportion of participants experiencing an adverse event, will be analysed as the other exploratory outcomes with Fisher’s exact test and logistic regression, adjusted by the protocol-specified stratification variable (the result of the latter test is the primary of the two tests). Adverse events will also be reported according to type, severity, and probable relation to the interventions for the two intervention groups.

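### The adverse-event test between arms is not limited to events collected the same way in both arms, although the experimental arm has an extra collection window

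*Protocol article*

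**What the plan says.** **Collection.** The protocol article, Exploratory clinical outcomes, sets out when events, serious or otherwise untoward, are recorded: they "will be gathered during the intervention for the intervention group and at post-treatment for both the control and the intervention groups". Table 1 has a row for "Adverse events" with marks in the during-trial column and at the week-10 interview. It names no arm and has no mark at week 37.

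**Contact between baseline and week 10.** Support person and support manual states: "Each trial participant is contacted over the telephone by a support person once a week during the 9 weeks of intervention". Feasibility outcomes shows who is meant: "the compliance will be assessed during the weekly telephone calls with the experimental participants". The abstract likewise places the weekly calls in the intervention group and says that controls receive no intervention. Under Blinding, the support person knows the allocation, whereas symptoms and recovery at the final interview are rated by blinded assessors.

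**Analysis.** Table 2 lists "Number of participants with one or more adverse event", with source *Interview*, to be compared by Fisher's exact test and by logistic regression adjusted for the stratification variable, the latter being primary. The text after Table 2 repeats that this outcome, "as well as the proportion of participants experiencing an adverse event, will be analysed as the other exploratory outcomes".

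**Scope of events.** The abstract counts severe adverse events. Exploratory clinical outcomes begins with serious and other untoward events that lead to hospital admission, threaten life or cause death, and then adds: "All adverse and untoward events will be categorised and summated". Table 2 counts any adverse event.

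**The concern.** Each participant counts once if any event is recorded, so the outcome depends on how often and how closely people are observed. A second collection window in one arm gives that arm more chances to record a first event. Neither Fisher's test nor adjustment for the diagnostic stratum can correct for unequal detection.

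If events from the extra window enter the count, a difference could appear with no true difference in risk, and a real excess among untreated controls could be masked. The abstract's objective is a feasibility assessment of benefits and harms, and p values below 0.05 are used to select outcomes for later hypotheses. A detection artefact could therefore be carried into the planning of a larger trial as a harm signal.

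The varying scope matters for the same reason. A hospital admission is unlikely to be forgotten over ten weeks, but a minor event may be.

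**Working it through.** The document states no figure for this outcome, so there is nothing to reproduce. The check has two parts.

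**1. Reading the sections together**

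| Element | Experimental arm | Control arm |
|---|---|---|
| Events gathered during the intervention | Yes | No |
| Events gathered at week 10 | Yes | Yes |
| Weekly telephone contact | Yes, by an unblinded person | None described |
| Counted in the between-arm test | Not restricted by source | Not restricted by source |

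Participants who miss week 10 add to the imbalance. A control who misses it contributes no event data, while an experimental participant who misses it may still have events on record from the treatment period.

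**2. Illustration of size**

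Inputs from the document: 1:1 allocation of 64 participants, so 32 per arm; two-sided tests at 0.05. Assumed inputs, none given in the document: the true risk of at least one event (equal in both arms) and the detection probability in each arm.

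Formulas: recorded proportion = true risk × detection; OR = [p_E/(1 − p_E)] / [p_C/(1 − p_C)]. The Fisher rejection rate comes from exact enumeration of two binomials with n = 32.

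Main case: p_E = 0.30 × 0.90 = 0.27 and p_C = 0.30 × 0.60 = 0.18. Then OR = (0.27/0.73)/(0.18/0.82) = 0.3699/0.2195 = 1.68. The expected excess is 32 × 0.09 = 2.9 participants.

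| True risk | Detection E / C | Recorded E / C | OR | Fisher p < 0.05 |
|---|---|---|---|---|
| 30% | 90% / 90% | 27% / 27% | 1.00 | 2.8% |
| 30% | 90% / 75% | 27% / 22.5% | 1.27 | 4.1% |
| 30% | 90% / 60% | 27% / 18% | 1.68 | 8.6% |
| 30% | 90% / 40% | 27% / 12% | 2.71 | 23% |
| 5% | 95% / 47.5% | 4.8% / 2.4% | 2.05 | 0.2% |

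In the last row the rejection rate is the same as with equal detection (0.2%), although the odds ratio is distorted.

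For the primary logistic model, an unadjusted score test served as a stand-in. With 19% recorded in the experimental arm and control detection half as good, it rejects 19.7% of the time, against 5.1% with equal detection.

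Over a wider assumed grid (recorded experimental proportion about 5% to 57%, control detection 0.5 to 0.9 relative to experimental), the spurious OR runs from 1.12 to 3.33 and the risk difference from 0.5 to 28.5 percentage points. The direction is always towards more apparent harm in the experimental arm. At the mild end (about 5% recorded, relative detection 0.9), the difference is 0.5 points, or 32 × 0.005 ≈ 0.2 participants.

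**The case against.** The strongest defence is that the tested outcome may already be symmetric. Table 2 names *Interview* as its source. Elsewhere in the article that word means the initial, final or end-of-trial interview, while the weekly contacts are described as telephone contacts or calls. Table 2 uses the same label for outside psychological treatment, which has to be ascertained in both arms. On this reading the test uses week-10 events, and events from the treatment period serve only the descriptive report by type, severity and relation. This is a reasonable reading, and it rules out calling the comparison biased as a settled fact. It does not close the point: the text never states the restriction, and both Table 1 and Exploratory clinical outcomes include the treatment-period collection.

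A reader might also infer that events are solicited in up to nine weekly calls. The article does not say this. It describes the calls as securing compliance and helping adherence, about ten minutes each, and the support manual is not shown. The extra collection window is explicit; that the calls are its channel is an inference.

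Read literally, the sentence that each trial participant is phoned weekly could cover controls too. The abstract and Feasibility outcomes confine the calls to the experimental arm, so this does not restore symmetry.

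Finally, harms play no part in the two feasibility success criteria, and the p values only screen for hypotheses. That stands, and it limits the consequence.

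**Conclusion.** The point holds in conditional form. The article fixes an unequal collection schedule and a between-arm test without saying that the test uses only events elicited alike. If events from the treatment period are counted, the comparison is biased towards apparent harm in the experimental arm. If *Interview* means week 10 only, what remains is an unstated restriction that one sentence would supply.

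The size cannot be derived from the document. The odds ratios of 1.27 to 2.71 are arithmetic on assumed detection rates and an assumed 30% risk; they are not estimates for this trial. The bias would be small for serious events and larger for minor ones, which the Table 2 count includes.

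A reader might infer that the trial's assessment of harms is invalid and must be corrected before anything else. The documents do not support that, because this is one exploratory outcome in a feasibility trial. It should be fixed. The inconsistent event definition is a separate wording fault to correct at the same time; it is not evidence of bias.

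**What to change.** 1. In Exploratory clinical outcomes and Table 2, state that the between-group test uses only events elicited at the week-10 interview by the blinded assessor, with the same structured questions covering weeks 0 to 10 in both arms. Blinding currently mentions only symptoms and recovery, so name adverse events there as well.
2. Report events recorded during the intervention in the experimental arm separately and descriptively, so that no safety information is lost. A source field on the event form is enough.
3. Use one event definition in the abstract, Exploratory clinical outcomes and Table 2. If both serious and all events are wanted, name them as two outcomes.
4. Report by arm the number of participants without a week-10 interview.

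The cost is a few sentences and one form field. There are two limits. Participants who miss week 10 give no comparative harm data, and this may not be a trivial loss: Background reports dropout of 50% against 20% in the earlier Danish trial. In addition, weekly contact may prime recall at week 10 in the experimental arm, so the restriction reduces the asymmetry without certainly removing it. This should be named as a limitation.

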**Methods and design:**

We will conduct an investigator-initiated, feasibility randomised controlled trial. Sixty-four participants are expected to be recruited via an advertisement posted on the homepage of the Student Counselling Service in Denmark. The inclusion criterion for participation in the trial will be the presence of anxiety disorder as assessed with the Mini International Neuropsychiatric Interview. The exclusion criteria will be suicidal risk, an ongoing episode of bipolar disorder or psychosis, concurrent psychological treatment for the anxiety disorder, considered unable to attend the intervention as planned (due to vacation, work/study placement, sickness, or similar occurrences), or lack of informed consent. The intervention group will be offered nine sessions with the ICBT programme FearFighter™ and a weekly telephone contact to support compliance. The control group will receive no intervention. We define the feasibility outcomes as follows: the fraction of randomised participants out of the eligible people (the lower 95 % confidence interval (CI) ≥ 50 %); and the fraction of compliant participants (those receiving at least six out of nine sessions) in the intervention group (the lower 95 % CI ≥ 60 %). The exploratory clinical outcomes are the number of participants no longer meeting the diagnostic criteria for an anxiety disorder at the end of the trial and level of distress (Beck Anxiety Inventory, Symptom Checklist-90-R, WHO Well-Being Index, Sheehan Disability Scale); the number of severe adverse events; and the occurrence of any psychological treatment outside the trial.

To prevent bias in design, and in the gathering and analysis of data throughout the trial, we will follow the SPIRIT 2013 statement which defines standard protocol items for clinical trials.

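### The between-arm adverse event test is not expressly limited to the week-10 collection that both arms share, although the experimental arm is also monitored during treatment

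*Protocol article*

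**What the plan says.** **Collection.** The last paragraph of Exploratory clinical outcomes says that serious and other untoward events "will be gathered during the intervention for the intervention group and at post-treatment for both the control and the intervention groups". Table 1 agrees that there are two collection points: its row "Adverse events" is marked in the during-trial column and at week 10. The table is not split by arm.

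**Analysis.** Table 2 lists "Number of participants with one or more adverse event", gives the source only as *Interview*, and plans Fisher's exact test plus logistic regression adjusted for the stratification variable, the latter being primary. The Statistical analyses text repeats that "the proportion of participants experiencing an adverse event, will be analysed as the other exploratory outcomes". Neither place gives a time point for the events that enter the test.

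**Which events.** The Abstract names "the number of severe adverse events". Exploratory clinical outcomes says that serious adverse events and other "untoward events that require hospitalisation, are life-threatening, or result in death are collected", and in its next sentence: "All adverse and untoward events will be categorised and summated". Table 2 counts any adverse event, and Statistical analyses adds reporting by type, severity and probable relation to the intervention.

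**Contact between week 0 and week 10.** Participants are "contacted over the telephone by a support person once a week during the 9 weeks of intervention" (Support person and support manual). The section concerns support for FearFighter, and the same person supports the 32 experimental participants. The control group receives no intervention. The Blinding section says that the support person knows the allocation and that the final interview is done by blinded assessors.

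**The concern.** A comparison of event proportions is fair only if both arms have the same chance of having an event recorded. Here one arm has an additional collection period. If events noted during treatment are pooled with those elicited at week 10, the experimental arm can show more participants with events even when the true risks are equal, because controls have only one occasion on which to remember and report. Blinded assessment at week 10 does not correct for records already made in one arm.

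The definition of an event decides how much this matters. A hospitalisation or a life-threatening event is unlikely to be missed by a single question at week 10. A passing worsening of symptoms is easily forgotten.

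Harms are part of the objective stated in the Abstract, and Statistical analyses uses p < 0.05 to select outcomes for later hypotheses. A spurious harm signal could therefore be carried into the planning of a larger trial.

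**Working it through.** The article gives no adverse event rate, detection rate or power for this outcome, so there is no figure of its own to reproduce. The check has two parts.

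**1. Which records feed the test?**

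- Pointing to week 10 only: Table 2 gives *Interview* as the source. Table 1 uses that word for the week-0 and week-10 visits, while the weekly contacts are called telephone contacts or calls.
- Pointing to pooling: Table 1 marks adverse events during the trial as well, and the outcomes text says that all events are summed, with no separation by collection point.
- Deciding sentence: none in the outcomes text, Table 2 or the Statistical analyses text.

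Both readings remain open.

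**2. How large could the effect of pooling be?**

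Inputs from the article: 64 participants allocated 1:1, hence 32 per arm; two-sided p < 0.05. Assumed inputs: true risk r, equal in both arms; detection d_E = 90 % of affected participants in the experimental arm; detection d_C = 50 % in controls, range 40 to 80 %.

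Observed risks are r × d_E and r × d_C. The expected counts are 32 times these. At r = 30 %: 32 × 0.30 × 0.90 = 8.6 experimental against 32 × 0.30 × 0.50 = 4.8 control. At r = 10 % they are 2.9 v 1.6, and at r = 50 % they are 14.4 v 8.0. The spurious risk ratio is d_E / d_C = 0.90 / 0.50 = 1.8 at every risk.

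The probability of p < 0.05 is the sum, over all 33 × 33 possible pairs of counts, of the product of two binomial probabilities wherever the test is significant. For Fisher's exact test:

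| True risk | 90 % v 90 % | 90 % v 80 % | 90 % v 50 % | 90 % v 40 % |
|---|---|---|---|---|
| 10 % | 0.009 | 0.009 | 0.015 | 0.020 |
| 30 % | 0.028 | 0.033 | 0.143 | 0.229 |
| 50 % | 0.032 | 0.045 | 0.305 | 0.485 |

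At 5 % true risk the value is 0.001 under both 90 % v 90 % and 90 % v 50 %. At 90 % v 70 % it is 0.052 at 30 % risk and 0.089 at 50 %.

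Table 2 makes logistic regression primary. As an approximation I used the Wald test of the unadjusted log odds ratio, with the stratum not modelled and tables with a zero cell counted as not significant:

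| True risk | 90 % v 90 % | 90 % v 80 % | 90 % v 50 % |
|---|---|---|---|
| 10 % | 0.008 | not used | 0.008 |
| 30 % | 0.043 | 0.050 | 0.184 |
| 50 % | 0.059 | 0.078 | 0.391 |

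**With the week-10 collection alone**, detection is the same in both arms. At 50 % in each, Fisher's test gives 0.019 at 30 % risk and 0.027 at 50 %, so the inflation disappears if week-10 recall is equal.

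**The case against.** The strongest reply is that the plan already does the right thing. On the usage in Table 1, *Interview* in Table 2 most naturally means the week-10 visit. The row above it in Table 2, psychological treatment during the 9 weeks, has the same source and covers both arms. On that reading the test is balanced and the in-treatment records serve monitoring only. This stands as a plausible reading, and it rules out the stronger inference that the plan prescribes a biased test. It does not close the point, because Table 1 also marks collection during the trial and no sentence says which records are tested.

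A reader might also infer that the allocation-aware support person collects events in the weekly calls. The article does not say so, and such operational detail may properly be left to the full protocol. The point does not need it: the unequal schedule is stated outright.

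A reader might further infer that the event definitions contradict each other. Mostly they do not. They can be read as nested, non-serious events are evidently in scope since events are to be reported by severity, and *severe* in the Abstract is loose wording in a summary. What stands is narrower: the sentence on what is collected covers fewer events than Table 2 counts. The timing sentence also speaks of serious and other untoward events. If the threshold of hospitalisation, threat to life or death carries over to it, the imbalance is negligible.

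Finally, 90 % v 50 % lies towards the pessimistic end of the assumed range. At 90 % v 80 %, Fisher's test stays below 0.05. That is correct and limits what can be claimed about size.

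**Conclusion.** The point holds as an open question in the plan with an easy remedy. The collection schedule is unequal by the article's own statement, and nothing expressly restricts the between-arm test to what both arms share. If in-treatment events are pooled, and if the additional collection finds events that a single question at week 10 would miss, the comparison is biased against FearFighter.

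The size is unknown. Under the assumed detection rates it ranges from nothing, for rare or serious events, to a clear excess of false signals for common non-serious events with poor recall in controls. When controls recall nearly as well, it is small.

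The trial's conclusions on feasibility are not threatened. The Discussion rests success on the share of eligible people randomised and on completion of FearFighter. Adverse events are one exploratory outcome whose p value only selects hypotheses.

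**What to change.** 1. In Exploratory clinical outcomes and in the adverse event row of Table 2, state that the between-arm test counts only participants with an event elicited by the same questions at the week-10 interview in both arms. If *Interview* already means this, one sentence settles it.
2. Report events noted during treatment separately and descriptively for the experimental arm, without a test.
3. As a minor wording point, let the collection sentence say that all adverse events are collected and that those requiring hospitalisation, threatening life or causing death are flagged as serious. Replace *severe* in the Abstract to match Table 2.

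The cost is wording only, with no new visit, instrument or participant. A few known events leave the comparative count, though they are still reported. Earlier questioning may sharpen recall in the experimental arm, so the imbalance is reduced rather than removed. At week 10 the harms questions should come after the diagnostic rating, so that answers about the programme do not unblind the assessor beforehand. Keeping all known events in the comparison and stating the difference in ascertainment is an alternative, but it leaves the p value hard to interpret.
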